## Methods

### Study design

This is a parallel group, randomised controlled trial, where participants will be randomly allocated into three groups; knee moment biofeedback group, gait pattern biofeedback group and control group. In participants with bilateral KOA, the most painful knee will be studied. The primary outcome will be KAM, while knee pain and functional ability will be considered secondary. All other outcomes will be exploratory outcome variables. The primary comparison will be between gait pattern feedback group and control group, while the comparison between gait pattern feedback group and knee moment feedback group will be exploratory.

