### Randomisation

After the baseline assessment, participants will be randomly allocated (2:2:1) to the knee moment biofeedback group, gait pattern biofeedback group or control group, using a block randomisation plan by the researcher. Blinding is not achievable in this intervention study, and therefore neither participants nor researcher will be blinded.

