#### Biomechanical outcomes

Across all groups, we will collect the biomechanical outcomes measures listed below in all three assessment sessions (weeks 0, 6 and 9). In the intervention groups, we will collect all these measures during training sessions 1 and 6, while training sessions 2–5 will only record knee loading and gait pattern data (no muscle activation data). For the control group, all these measures will only be recorded during sessions 1 and 6.*Knee loading data* will be collected and calculated as KAM, KFM and KAM impulse. Hip moment will also be calculated as exploratory information.*Gait patterns data* will be collected as FPA, step width, and step length. Other gait parameter such as trunk lean and pelvis tilt will also be calculated.*Muscle activations data* will be measured by surface EMG from lower limb muscles using surface electrodes. Before placement, electrode locations on each participant’s affected leg will be palpated, shaved, lightly abraded, and cleaned with an alcohol swab. EMG normalisation will be performed using maximum voluntary contraction (MVC) tests for all these five muscle groups (knee extension, knee flexion, ankle plantar flexion, ankle dorsiflexion, hip abduction).

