### Overview of the programme

Participants in the intervention groups will attend the lab a total of nine times, while the control group will attend a total of seven times. Firstly, all participants will attend the baseline assessment session (week 0a), after which a randomisation procedure will be carried out where participants will be randomly allocated to each group. Then, participants in the intervention groups will attend a biofeedback identification session in the same week (week 0b) to identify their optimal gait patterns. From week 1 to week 6, participants will start the weekly gait training sessions. Intervention groups will have real-time biofeedback along with treadmill walking, while the control group will perform treadmill walking for the same length of time without any instruction or feedback. The last training session (week 6) will finish with the post-training assessment session. Finally, a retention assessment session will be carried out one month later (week 10) for the two intervention groups only. Between the post-training assessment session (week 6) and follow-up assessment session (week 10), there will be no training or instructions of any kind provided. Figure 1 details the trial flow chart.

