### Assessment sessions

There will be three assessment sessions (Fig. 1) throughout the programme (week 0, 6 and 10). All three assessment sessions will be identical, except the Oxford Knee Score assessment will be performed in the baseline assessment session (week 0). The WOMAC questionnaire will be assessed at the beginning of each assessment session, after which, reflective markers and EMG electrodes will be attached to the participant. Overground walking, stair ascent and descent, and sit-to-stand will be performed in a block randomised order. All activities will be performed under their preferred overground gait condition, and each activity will be repeated five times. The overground walking speed during each assessment session will be controlled to be within 20% of the baseline overground walking speed. At the end of the final trial of each activity, participants will be asked to report their perceived knee joint pain using NRS.

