### Data management and confidentiality

The University of Bath will act as the Data Controller for this study. Only the researcher team members will have access to the data. Personal information will never be identifiable in published papers or conference presentations. Data and participants information will be collected in accordance with the confidentially NHS Code of Practice and all information will be subject to the current conditions of the Data Protection Act. Each participant will be assigned a unique project code which will be used to identify the participant anonymously. An Excel data sheet maintained on a University X: Drive (password protected) will be used to record participant information. Signed consent form will be stored in a locked cupboard and kept for 10 years to evidence the consent process.

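### The Randomisation section rules out blinding for a reason that covers only participants and trainers; masked processing of the primary KAM data is feasible but forgone

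*Protocol article*

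**What the plan says.** - **Blinding.** Methods, Randomisation: "Blinding is not achievable in this intervention study, and therefore neither participants nor researcher will be blinded". No other section describes a masked assessor, data processor or analyst.
- **Who allocates.** The same section has allocation done after the baseline assessment, "using a block randomisation plan by the researcher". The person who is not blinded therefore also assigns the arm.
- **Primary outcome.** Study design: "The primary outcome will be KAM, while knee pain and functional ability will be considered secondary". The Statistical analysis section adds KAM impulse, and its example model uses first-peak KAM. Primary success rests on the KAM change from week 0 to week 6.
- **How KAM arises.** Biomechanical outcomes: knee loading data "will be collected and calculated as KAM, KFM and KAM impulse". Experimental setting gives the sources as optical motion capture and force platforms. Assessment sessions has each activity repeated five times.
- **Week 6 setting.** Overview of the programme: "The last training session (week 6) will finish with the post-training assessment session".
- **Pain.** Assessment sessions: "participants will be asked to report their perceived knee joint pain using NRS".
- **Existing coding.** Data management and confidentiality: "Each participant will be assigned a unique project code which will be used to identify the participant anonymously". Study management and safety describes a supervisory team, distinct from the lead researcher, that already audits data storage.

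**The concern.** The statement gives one reason and draws a conclusion wider than that reason supports. People who see feedback graphs, and people who run the feedback, must know the arm. A stored file of marker trajectories and ground reaction forces need not carry the arm or the visit.

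KAM is calculated from such files after the visit. In marker-based gait analysis, some judgement usually comes between recording and result, such as cleaning marker data, marking gait events and accepting trials. The article does not list these steps, so their presence here is an inference. If they are taken by someone who knows the arm and expects a reduction, the primary outcome can drift towards the expected result. By declaring blinding out of reach, the plan gives up a safeguard it has the means to apply.

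**Working it through.** **1. Does the reason cover each role?**

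| Role | Must know the arm? | Basis in the article |
|---|---|---|
| Participant | Yes | Feedback is on screen, or absent for controls |
| Person delivering training | Yes | Runs the feedback session |
| Staff present at week 6 assessment | Yes, as planned | Assessment closes the last training visit |
| Processor of KAM files | No | KAM is calculated from recordings; processor not named |
| Analyst of KAM values | No | Not named |

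The reason supports the first two rows. The third follows from the visit schedule. The last two are not covered by it.

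**2. Which files could be affected?** Baseline recordings are made before allocation, so their collection cannot be influenced by the arm. Nothing stops them being processed later, when the arm is known. Week 6 recordings are collected and processed after allocation. Success is a change between the two visits, so processing at either end can matter.

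**3. Are the means at hand?** Participants already have project codes, and a supervisory team could hold a second key. That second key is needed because the unblinded researcher would recognise the ordinary project code.

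**4. The plan's own figure (context only).** With d = 1.01, two-sided alpha 0.05 and power 0.80, a two-sample t test with equal groups needs 16.4 per group, rounded up to the stated 17. Masking changes neither this number nor alpha.

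**5. Illustration of size.** The documents give no figure for processing bias, so the shift b is an assumption, in SD units of the compared quantity.

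- Groups: 20 (gait pattern) and 10 (control), from Study population/sample size.
- SE = sqrt(1/20 + 1/10) = 0.387 SD; df = 20 + 10 − 2 = 28.
- Noncentrality = b / SE. The rejection rate comes from the noncentral t distribution, two-sided 5%, with no true effect.

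| Assumed shift b | Noncentrality | Type I error, 20 v 10 | Type I error, 16 v 8 (after 20% dropout) |
|---|---|---|---|
| 0 | 0 | 5.0% | 5.0% |
| 0.1 SD | 0.26 | 5.7% | 5.6% |
| 0.2 SD | 0.52 | 7.9% | 7.3% |
| 0.3 SD | 0.77 | 11.6% | 10.2% |

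For scale, 0.2 SD is 0.2 / 1.01, about one fifth of the planned effect. The table uses a simple t test, whereas the plan uses a mixed model, so it shows order of magnitude only.

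**The case against.** **The sentence names only participants and the researcher.** On this view a separate masked processor is simply not mentioned, and a condensed article may leave processing to the full protocol. Part of this stands: a missing processing pipeline, trial-averaging rule or rejection rule is no finding. But the opening clause says blinding as such cannot be achieved, and the researcher is the only operator described. That is a stated position, not silence.

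**The processor and the judgement steps are not in the article.** This stands. A reader might infer that KAM is known to be processed by staff aware of the arm. The documents make that a fair inference, not a fact.

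**Masking would be partial.** This also stands. Week 6 markers are placed, and trials recorded, by staff who know the arm. Altered foot angle or step width may hint at the arm in the files. The Overview reserves week 10 for the intervention groups, so an identifiable week 10 file would point to a non-control unless the visit label is removed. Partial masking still removes avoidable discretion in processing.

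**Pain.** A reader might infer that pain ratings are also generated by unblinded staff. The documents do not support this: participants report the rating themselves, and no interview is described. The main risk for pain is that participants know their own arm, which masked processing cannot change.

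**Small sample.** A reader might think that 30 people make a small shift more damaging. For the error rate, the reverse holds. At 200 v 100, SE = sqrt(1/200 + 1/100) = 0.122, noncentrality = 0.2 / 0.122 = 1.63, and a 0.2 SD shift would give about 37%, against 7.9% at 20 v 10.

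**Conclusion.** The point holds for KAM processing and analysis. The Randomisation section dismisses blinding for a reason that does not extend to calculating the primary outcome from recorded files. Masked processing is feasible with the codes and team already described, and nothing in the article provides it.

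It does not show that KAM will be biased. The conclusion rests on two inferences: that the unblinded researcher, or someone equally aware of the arm, processes the files, and that processing involves some discretion. The error rates of 5.7% to 11.6% follow only from assumed shifts of 0.1 to 0.3 SD and are not estimates for this trial. Nor does the article present KAM as objective or immune to bias, so it should not be faulted for that. This is a low-cost improvement to an openly disclosed limitation, and it leaves the sample size and significance level unchanged.

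**What to change.** Replace the blinding sentence in the Randomisation section with:

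> Participants and the researcher delivering training cannot be blinded. Week 0 and week 6 assessment files (and week 10 where collected) will be renamed with random codes by a member of the supervisory team, processed in mixed order with arm and visit removed, using trial-rejection criteria set beforehand, and KAM values will be locked before the group key is released.

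KAM impulse should be handled in the same way, since the Statistical analysis section also names it as primary. Locking before release matters more than hiding group labels in the analysis, because the 2:1 group sizes would give the arms away.

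Cost: some recoding work by existing team members, and processing delayed until files are batched. No extra assessor, visit or participant is needed. The report should say that masking was incomplete because of week 6 marker placement and visible gait changes, and should describe pain as self-reported by unblinded participants.

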### Experimental setting

All sessions will be conducted in the Applied Biomechanics Suite at the University of Bath. During gait retraining sessions, participants will walk on an instrumented treadmill. During assessment sessions, participants will perform overground walking, sit-to-stand and stair climbing on force platforms embedded in the floor and a portable force platform embedded on the first step of a two-step stair. During each session, a twelve camera, three-dimensional optoelectronic camera system (Arqus and Miqus, Qualisys, Sweden) will be used to collect motion capture data. Reflective markers will be placed on the distal phalanx of the first toe, metacarpal phalangeal joints 1 and 5, calcaneus, tuberosity of 5th metatarsal, sustentaculum tali of calcaneus, lateral apex of the peroneal tubercle, medial and lateral malleolus of the ankle, tibial tuberosity, medial and lateral femur epicondyles, left and right anterior superior iliac spine and posterior superior iliac spine, left and right iliac crest, vertebrae C7, suprasternal notch of the manubrium and left and right acromion process. Four marker clusters on rigid plates will be placed on the lateral side of the shank and thigh of each leg. Lower limb muscle activation data will be collected by surface electromyography (EMG), including vastus lateralis, vastus medialis, rectus femoris, biceps femoris, medial gastrocnemius, soleus, tibialis anterior, and gluteus medius.

### Outcome measures

#### Demographics

Age, sex, and previous injury/surgery history will be asked at the baseline assessment session (week 0), along with weight and height measurements.

#### Qualitative assessment

The Oxford Knee Score questionnaire will be carried out only at baseline assessment session (week 0), as a reference of the baseline severity of KOA. The Western Ontario and McMaster Universities Arthritis Index (WOMAC) will be assessed at all three assessment sessions (weeks 0, 6 and 10) to evaluate the condition of KOA, including pain, stiffness, and physical functioning of the knee joint. Numeric Rating Scale (NRS) of pain on the target knee joint will be assessed after the final trial of each activity at all assessment sessions (week 0, 6 and 10).

#### Free-living energy expenditure

All participants will be asked to wear a wrist-mounted physical activity monitor (GENEActive accelerometer) continuously for 6 weeks from the baseline assessment session (week 0 – 6). Free-living energy expenditure will be estimated using previously published algorithms [32]. Weekly activity log will be used from one week prior to the first training session till the end of the training (week 0 – 5). Participants will record the type of activity, duration, intensity/frequency and how they feel every day for 6 weeks.

#### Biomechanical outcomes

Across all groups, we will collect the biomechanical outcomes measures listed below in all three assessment sessions (weeks 0, 6 and 9). In the intervention groups, we will collect all these measures during training sessions 1 and 6, while training sessions 2–5 will only record knee loading and gait pattern data (no muscle activation data). For the control group, all these measures will only be recorded during sessions 1 and 6.*Knee loading data* will be collected and calculated as KAM, KFM and KAM impulse. Hip moment will also be calculated as exploratory information.*Gait patterns data* will be collected as FPA, step width, and step length. Other gait parameter such as trunk lean and pelvis tilt will also be calculated.*Muscle activations data* will be measured by surface EMG from lower limb muscles using surface electrodes. Before placement, electrode locations on each participant’s affected leg will be palpated, shaved, lightly abraded, and cleaned with an alcohol swab. EMG normalisation will be performed using maximum voluntary contraction (MVC) tests for all these five muscle groups (knee extension, knee flexion, ankle plantar flexion, ankle dorsiflexion, hip abduction).

### Overview of the programme

Participants in the intervention groups will attend the lab a total of nine times, while the control group will attend a total of seven times. Firstly, all participants will attend the baseline assessment session (week 0a), after which a randomisation procedure will be carried out where participants will be randomly allocated to each group. Then, participants in the intervention groups will attend a biofeedback identification session in the same week (week 0b) to identify their optimal gait patterns. From week 1 to week 6, participants will start the weekly gait training sessions. Intervention groups will have real-time biofeedback along with treadmill walking, while the control group will perform treadmill walking for the same length of time without any instruction or feedback. The last training session (week 6) will finish with the post-training assessment session. Finally, a retention assessment session will be carried out one month later (week 10) for the two intervention groups only. Between the post-training assessment session (week 6) and follow-up assessment session (week 10), there will be no training or instructions of any kind provided. Figure 1 details the trial flow chart.

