## Abstract

**Background:**

Gait retraining is a common therapeutic intervention that can alter gait characteristics to reduce knee loading in knee osteoarthritis populations. It can be enhanced when combined with biofeedback that provides real-time information about the users’ gait, either directly (i.e. knee moment feedback) or indirectly (i.e. gait pattern feedback). However, it is unknown which types of biofeedback are more effective at reducing knee loading, and also how the changes in gait affect pain during different activities of daily living. Therefore, this study aims to evaluate the acute (6 weeks of training) and chronic (1 month post training) effects of biofeedback based on personalised gait patterns to reduce knee loading and pain in people with knee osteoarthritis, as well as examine if more than one session of knee moment feedback is needed to optimise the gait patterns.

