### Delayed control intervention

While control participants may have a strong preference to receive the intervention, they will be offered a delayed control intervention after they finish the study (Week 6). It will involve a biofeedback identification session and six in-person biofeedback gait retraining sessions.

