### Statistical analysis

Study outcomes will be assessed quantitatively. The primary outcome will be KAM and KAM impulse, while NRS pain and WOMAC scores will be considered secondary. All other biomechanical outcomes (e.g. spee, EMG data, gait pattern variables) will become exploratory outcome variables in nature. The primary success of the trial will be based on a comparison of KAM reduction between week 0 and week 6, while the success of retention will be based on a comparison of between week 0 and week 10. In the knee moment feedback group, gait pattern changes (FPA, step width and step length) from week 1 to week 6 and 1-month follow-up will be compared to explore the evolvement of the gait pattern in response to knee moment feedback intervention. The proportion of participants adequately completing the programme and the average number of training sessions completed will be reported.

All outcomes will be analysed using the intention-to-treat approach and thus we will include data from all enrolled participants, regardless of dropout. Descriptive statistics will be used to compare participants randomised into the two intervention groups and a control group with respect to baseline variables. Continuous variables will be expressed as the means and standard deviations (if normally distributed). The data normality and sphericity will be tested using Shapiro–Wilk test and Mauchly’s test respectively. Linear mixed effect (LME) models will be used to evaluate whether knee loading variables, knee pain score and WOMAC score significantly differ between the three time points (week 0, week 6 and week 10), with group as fixed effect, and participant (repeat measures) as a random effect. LME will be used for our primary objective to explore the difference between baseline assessment (week 0) and post-intervention assessment (week 6) with comparison of gait pattern group and control group, and the secondary objective to explore the gait pattern difference across all time points in knee moment group. The example LME formula for comparison between the gait pattern and control group within MATLAB is stated as below:$${\text{glme}}\_\mathrm{KAM }=\mathrm{ fitglme}({\text{data}},\mathrm{ ^{\prime}}{\text{KAM}}1 \sim \mathrm{ Group }+\mathrm{ timepoint }+\mathrm{ timepoint}*\mathrm{Group }+ (1|{\text{Participant}})\mathrm{^{\prime}},\mathrm{ ^{\prime}}\mathrm{FitMethod^{\prime}},\mathrm{^{\prime}}\mathrm{Laplace^{\prime}})$$

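### Retention is judged from week 0 to week 10, but control has no week-10 assessment, so the plan supports no controlled claim of a lasting effect, and its sections disagree on who is assessed and when

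*Protocol article*

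**What the plan says.** **Who attends week 10.** Overview of the programme states that "a retention assessment session will be carried out one month later (week 10) for the two intervention groups only". It gives the intervention groups nine visits, "while the control group will attend a total of seven times". Under Delayed control intervention, control participants are told "they will be offered a delayed control intervention after they finish the study (Week 6").

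**The conflicting text.** Biomechanical outcomes says: "Across all groups, we will collect the biomechanical outcomes measures listed below in all three assessment sessions (weeks 0, 6 and 9"). It differs from the overview on which groups are assessed and on the week. Qualitative assessment and Assessment sessions both list weeks 0, 6 and 10 without excepting control.

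**The analysis.** Statistical analysis uses mixed models to ask whether knee loading, pain and WOMAC "significantly differ between the three time points (week 0, week 6 and week 10), with group as fixed effect". It does not leave control out. It then sets a criterion: "the success of retention will be based on a comparison of between week 0 and week 10". No comparator is named.

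**The aim.** The abstract says the study will "evaluate the acute (6 weeks of training) and chronic (1 month post training) effects of biofeedback".

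**The primary criterion** is separate: "The primary success of the trial will be based on a comparison of KAM reduction between week 0 and week 6". The written formula for gait pattern versus control covers baseline and post-training only.

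**The concern.** The protocol names a success criterion and a three-timepoint group model for a visit that control does not attend. The gap is planned and is not dropout, so neither the intention-to-treat statement nor a mixed model's tolerance of missing data can fill it. Control is also offered the feedback programme after week 6, so a later measurement would not be reliably untreated.

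At stake is what the trial may say about the month after training. A within-arm change from week 0 to week 10, in people who are not blinded, mixes any lasting effect of training with time trend and with growing familiarity with the laboratory, the markers and the tasks. The Background section itself acknowledges familiarisation. For NRS pain and WOMAC there is also regression to the mean, because entry requires current knee pain (NRS of at least 2). A reader who sees retention success beside the aim of chronic effects would take it as evidence of effectiveness, which this comparison cannot give.

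**Working it through.** **1. Visit counts (Overview of the programme).** The post-training assessment is part of the week-6 session.
- Intervention: baseline 1 + identification 1 + training 6 + week 10, 1 = 9, as stated.
- Control: baseline 1 + training 6 = 7, as stated. A week-10 visit would make it 8.

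The protocol's own counts therefore support the overview and not the all-groups sentence under Biomechanical outcomes.

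**2. What the week-10 model can estimate.** Write m(g,t) for the mean of group g at week t, with three groups and weeks 0, 6 and 10. A model with group, time and their interaction has 1 + 2 + 2 + 4 = 9 fixed parameters.

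| Data | Occupied cells | Rank |
|---|---|---|
| Control seen at week 10 | 9 | 9 of 9 |
| Control not seen at week 10 | 8 | 8 of 9 |

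The controlled retention effect would be [m(GP,10) − m(GP,0)] − [m(C,10) − m(C,0)]. It needs m(C,10), for which there are no data.

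With that cell empty:
- Not estimable: control week 10 minus week 0; gait pattern versus control change at week 10.
- Estimable: control week 6 minus week 0; gait pattern versus control change at week 6; week 10 minus week 0 within each feedback arm; gait pattern versus knee moment change at week 10.

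The primary two-group, two-timepoint model has rank 4 of 4.

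**3. The other reading of the model.** The three-timepoint sentence names group as a fixed effect but no interaction. With main effects only there are 1 + 2 + 2 = 5 parameters, and the eight occupied cells give rank 5 of 5, so the model fits. But the week-10 effect then comes from the feedback arms alone and is applied to control, and the group difference in change is zero by construction. This reading gives no controlled retention effect either.

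**4. Size of the problem for a within-arm criterion.** The protocol gives no power or error rate for week 10, so there is no stated figure to reproduce. As an illustration, take a paired t-test of week 10 against week 0, two-sided 0.05 (sidedness is not stated in the protocol), when feedback has no effect but the arm drifts by d SDs of the change score. The test statistic is non-central t with n − 1 degrees of freedom and non-centrality d√n. I use n = 20 (planned arm size) and n = 16 (20 × 0.8, after the stated 20% dropout). For n = 20 and d = 0.3, the non-centrality is 0.3 × √20 = 1.34.

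| Assumed drift d | n = 20 | n = 16 |
|---|---|---|
| 0 | 5% | 5% |
| 0.1 | 7% | 7% |
| 0.2 | 14% | 12% |
| 0.3 | 25% | 20% |
| 0.5 | 56% | 46% |

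The drift values are assumptions; the documents give none. These are rejections in either direction. With no drift, 2.5% are in the favourable direction; with favourable drift, nearly all are once d reaches 0.2.

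**The case against.** The strongest defence is that the design is coherent for what it calls retention. Control receives no feedback, so it has no trained gait to retain. The retention objective in the Background compares the two types of biofeedback, and both of those arms attend week 10. The primary objective is confined to the 6-week programme, and its formula uses two timepoints. The protocol never writes out a gait pattern versus control contrast at week 10.

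Much of this stands, and it rules out several stronger readings that a reader might infer:

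- *That the group model fails for control as a whole.* It does not. Only control at week 10, and contrasts that need it, are lost.
- *That the primary result is compromised.* It is not. Weeks 0 and 6 are complete by design in both arms of the primary comparison.
- *That only a before-after test is left at week 10.* The randomised contrast between the feedback arms is estimable and serves the stated retention objective. It cannot show that either type of feedback has a lasting effect against no feedback.
- *That regression to the mean threatens the retention result for KAM.* Participants are selected on pain, not on KAM, so the argument applies directly to NRS and WOMAC. For KAM the rival explanations are time trend and familiarity.
- *That false success is likely.* The illustration depends on the size and direction of the drift. At 0.1 SD the rate is barely above nominal, and an unfavourable drift of 0.3 SD would leave favourable success at about 0.1%. The planned analysis is also a mixed model and not a paired t-test.

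The defence does not answer two things. The sections contradict each other on who is assessed and in which week. And a success criterion with no comparator sits beside an aim of chronic effects, with nothing to tell the reader that control is absent.

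**Conclusion.** The point holds within these limits. The control week-10 mean and the gait pattern versus control change at week 10 cannot be estimated (rank 8 of 9 with the interaction), and a main-effects model only lends control the feedback arms' week-10 effect. A week 0 to 10 change within a feedback arm is therefore descriptive and cannot be read as effectiveness. How misleading it could be depends on a drift that this design cannot measure after week 6: about 7% to 56% rejections with 20 people for an assumed 0.1 to 0.5 SD.

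This should be fixed, but it does not threaten the trial's main result, since the primary week 0 to 6 analysis is not affected. The conclusion assumes that the overview, the visit counts and the delayed-intervention section describe the real schedule. If the all-groups sentence does, the empty cell disappears, but the overview and the visit counts are then wrong and the delayed offer after week 6 needs explaining.

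**What to change.** 1. Make Qualitative assessment, Biomechanical outcomes, Overview of the programme, Assessment sessions and Statistical analysis agree on which groups are assessed at the last session and on whether it is week 9 or week 10.
2. If control has no such session, state that control data enter at weeks 0 and 6 only, and restrict any model containing week 10 to the two feedback arms.
3. Report weeks 0 to 10 as a within-arm description plus the randomised contrast between the feedback arms, with the exploratory status that contrast already has.
4. Do not present retention success or chronic effects as effectiveness against control, and say in the aim and the analysis section that week 10 has no untreated comparator.

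The cost is wording and a model restriction. No visit, sample size or primary analysis changes. An added control visit would make the controlled contrast estimable, but it needs resources and bears on the timing of the delayed programme, so it is not requested here.
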